**11.2 Severity of Adverse Events**

Severity of AEs will be assessed according to the following definitions:

Mild: Awareness of event but easily tolerated

Moderate: Discomfort enough to cause some interference with usual activity

Severe: Inability to carry out usual activity, including play for infants and children.

**11.3 Causality of Adverse Events**

Causality of AEs, i.e. relationship to the trial treatment, will be assessed according to the following definitions:

| Unrelated | No evidence of any causal relationship |
| --- | --- |
| Unlikely | There is little evidence to suggest there is a causal relationship (e.g. the event did not occur within a reasonable time after administration of the treatment). There is another reasonable explanation for the event (e.g. the participant’s clinical condition, other concomitant treatment). |
| Possible | There is some evidence to suggest a causal relationship (e.g. because the event occurs within a reasonable time after trial treatment). However, the influence of other factors may have contributed to the event (e.g. the participant’s clinical condition, other concomitant treatments). |
| Probable | There is evidence to suggest a causal relationship and the influence of other factors is unlikely. |
| Definite | There is clear evidence to suggest a causal relationship and other possible contributing factors can be ruled out. |

**11.4 Serious Adverse Events (SAE)**

**Definition of SAE**

An SAE is defined as any adverse event that:

- Results in death
- Is life-threatening*
- Requires hospitalisation or prolongation of existing inpatient’s hospitalisation**
- Results in persistent or significant disability or incapacity
- Is a congenital abnormality or birth defect

* “Life-threatening” in the definition of “serious” refers to an event in which the participant was at risk of death at the time of the event; it does not refer to an event which hypothetically might have caused death if it were more severe.

** “Hospitalisation” means any unexpected admission to a hospital department. It does not

apply to scheduled admissions that were planned before study inclusion or visits to an accident and emergency department (without admission).

Medical judgement should be exercised in deciding whether an adverse event/reaction is serious in other situations. Important adverse events/reactions that are not immediately life-threatening, or do not result in death or hospitalisation but may jeopardise a participant, or may require intervention to prevent one of the other outcomes listed in the definition above should also be considered serious.

**11.5 Reporting of SAEs**

Rapid reporting of all SAEs occurring during the study must be performed as detailed in SAE reporting instructions. SAEs will be reported via the eCRF within 24 hours of becoming aware of the event. All reported SAEs will be reviewed by the Chief Investigator (or designee) within 2 working days of receiving notification of the SAE report. The SAE review will be recorded on the eCRF.

SAEs will be followed up until they are resolved.

If the investigator becomes aware of safety information that appears to be related to the treatment, involving a participant who participated in the study, even after an individual participant has completed the study, this should be reported to the Sponsor.

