**7. Trial Intervention**

**7.1 High treatment intervention**

*PFL* is a community-based home visiting programme (HVP) which aims to improve children’s school readiness skills by intervening during pregnancy and working with families until the children start school at age 4/5 years. The high treatment group will receive twice monthly home visits, lasting approximately one hour, delivered by mentors from a cross-section of professional backgrounds such as psychologists and family support specialists. Mentors will receive extensive training prior to programme implementation and monthly supervision thereafter to ensure fidelity to the programme model. Each family will be assigned the same mentor over the course of the intervention where possible. The mentors will use role modelling, demonstration, coaching, discussion, encouragement, and feedback to deliver the intervention, as well as direct interactions with the child in the presence of the parent. The aim of the visits are to support and educate the parents on key child rearing issues including the identification of developmental milestones and appropriate parenting practices that promote the children’s health, and cognitive and non-cognitive development. Each visit will be guided by a set of *PFL* ‘Tip Sheets’ which are based on pre-existing governmental and local non-governmental organisations’ recommendations, and present best-practice information on pregnancy, parenting, and child health and development. There are three sets of age-specific Tip Sheets - pre-birth-12 months, 1-2 years, and 2-4 years. There are approximately 150 *PFL* Tip Sheets as part of the programme’s curriculum. The mentors will be able to choose when to deliver the Tip Sheets within these specific time periods based on the age of the child and the needs of the family. The Tip Sheets will be given to the participants at the end of each visit to keep as an on-going resource.

The high treatment group will also be invited to participate in an additional parenting course (Triple P Positive Parenting Program; Sanders et al., 2003) when their children are between 2 and 3 years old i.e., after they have completed the 24-month assessment. Triple P promotes healthy parenting practices and positive parent-child attachment. The intervention will involve the delivery of Group Triple P which consists of 5 two-hour group discussion sessions and 3 individual phone calls facilitated by the mentors.

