**7.2 Low treatment intervention**

Both the high and low treatment groups will receive some common supports including developmental materials and book packs. The developmental packs will consist of materials such as a baby gym, food utensils, safety items and an assortment of developmental toys. Both groups will also be encouraged by letter and text message to attend public health workshops on stress management and healthy eating which are already taking place in the community. The low treatment group will also have access to a support worker who can help them avail of community services if needed, while this function will be provided by the mentors for the high treatment group.

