# 10.4 Assessments

**Timing:** Data will be collected from both the programme participants (both high and low treatment groups) and the external comparison group within the same time period. Baseline data will be collected after confirmation of informed consent/randomisation assignment and before the programme begins. Subsequently, data will be collected when the infants are 6, 12, 18, 24 months of age and then each subsequent year (36 & 48 months) until the study child starts school (at age 4/5). Records from the maternity hospitals will be collected after the birth of the child and records from the children’s hospital will be collected when the child is at least 4 years old. It is important to collect data more regularly during the early stages of the child’s development as the evidence based on US interventions e.g. the Early Head Start programme, found that interventions have the greatest impact between 12 and 18 months. In addition, more data points will help track developmental trajectories. In total, eight waves of data will be collected. As the data collection will be sequential, each family will be interviewed when the child is the same age.

**Informant*:*** A combination of data capture methods will be used to produce optimum quality data. The primary informant at household level will be the mother through CAPI interview. The father, if available and living in the household, will also be required to participate in a shorter self-administered interview. Based on a scoping survey we estimate that about 50% of children will have biological parents living apart. If contact details are available from the mother, the absent biological father will be contacted and asked to complete the self-administered questionnaire. Data will also be collected on any siblings in the household. These data are crucial for evaluation of the RCT component, as given the design of the programme a pre-test (i.e. a pre-test measures outcomes prior to service delivery to facilitate comparison with post programme outcomes), is not possible. Therefore examining the key outcomes of the siblings of the PFL children before the programme begins will allow us to determine whether the parents’ behaviour, and its subsequent effect on the PFL children, differs before and after PFL. Additionally, data will be collected from junior infant school teachers (using the early development Instrument).

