Survey Instruments*:* Table 1 below lists the complete set of instruments which will be collected over the 8 data assessment point. The assessments will be divided into two part – the primary child outcome measures and the secondary parent outcome measures. The parent information will include 1) Demographic/Household, 2) Employment/Income, 3) Pregnancy, 4) Parenting/Neglect, 5) Maternal Social Support, 6) Maternal Socio-emotional Functioning, 7) Maternal Health, 8) Maternal Drug/Alcohol Use, 9) the Home Environment, 10) Breastfeeding, 11) Childcare Decisions, 12) Maternal Cognitive Assessment, 13) General Questions, 14) Programme Satisfaction, 15) Open-ended Questions, 16) Sibling Behaviour. The child information will include 1) Child Development and 2) Child Health. The specific instruments for each domain are listed in Table 1.

Providing Feedback to Families after Assessment*:* The interviewer will end each interview sessions with a debriefing in which the interviewer will thank the respondents for their time and ask them if they have any questions and how they felt the interview went. If an assessment reveals that a child is above a certain level of clinical risk, in terms of developmental delay for example, we will inform the parents of this and write a letter referring them to the appropriate agency. It should be noted that this may bias the results of the impact evaluation if a significant number of children are at this level, however it is essential to maintain a balance between scientific rigor and ethical considerations.

**Maintaining Contact with Families Between Assessments*:*** The research team will maintain contact with the PFL families and the external comparison group between assessments using the Database Management System (DBMS) to enable contact with, and tracking of, participants. This system will be used to track the consent status and any contacts between the researchers and the PFL participants, as well as change of address or any other factors that may affect the researcher’s ability to carry out the evaluation. A lo-call number will also be maintained in order for families to contact the research team. In addition, a programme newsletter which talks about the importance of evaluating the programme and highlights some basic data findings may help the participant families to better connect with the research side of the programme.

[figure not shown]

[figure not shown]

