| Romantic Relationship Quality: *Relationship Quality Index* |  |  |  |  |  |  | X |  |
| **Maternal Health** | Mother’s Health as a Child | X |  |  |  |  |  |  |  |
| Mother’s Height & Pre-pregnancy Weight | X |  |  |  |  |  |  |  |
| Mother’s Current Weight |  |  | X | X |  |  |  |  |
| Mother’s General Health Status | X |  |  | X | X | X | X | X |
| Indicator for Mother has Long Term Illness | X |  |  |  |  |  |  |  |
| Existence and Type of Mother’s Physical Medical Conditions | X |  |  |  |  |  |  |  |
| Existence and Type of Mother’s Psychological Health Conditions | X |  |  |  |  |  |  |  |
| Indicator of whether Mother taking Prescribed Medication | X |  |  |  |  |  |  |  |
| Existence and Type of Family Psychological Conditions | X |  |  |  |  |  |  |  |
| Indicator for whether Mother has/ever had Medical Card | X |  |  |  | X |  |  |  |
| Indicator for whether Mother has/ever had GP Visit Card | X |  |  |  | X |  |  |  |
| Indicator for whether Mother has Private Health Insurance | X |  |  |  |  |  |  |  |
| **Category** | **Measure/Information Obtained** | **BL** | **3** | **6** | **12** | **18** | **24** | **36** | **48** |
| **Maternal Health**  ***(continued)*** | Mother’s Diet/Eating Habits | X |  |  | X |  |  |  |  |
| Mother’s Exercise Habits | X |  |  | X |  |  |  |  |
| Mother’s Health Services Use in last 12 months | X |  |  |  | X |  | X |  |
| Maternal Health since Birth of Baby |  |  | X |  |  |  |  |  |
| Maternal Health During Pregnancy |  |  | X |  |  |  |  |  |
| Mother’s Breathing |  |  | X |  |  |  |  |  |
| Mother’s GP Visits |  |  | X | X | X | X | X | X |
| Family Planning |  |  |  | X | X | X | X | X |
| **Maternal Drug/ Alcohol Use** | Mother’s Cigarette Use Before Pregnancy | X |  |  |  |  |  |  |  |
| Mother’s Reasons for Change in Cigarette Use During Pregnancy | X |  |  |  |  |  |  |  |
| Mother’s Alcohol Use Before Pregnancy (quantity & type) | X |  |  |  |  |  |  |  |
| Mother’s Reasons for Change in Alcohol Use During Pregnancy | X |  |  |  |  |  |  |  |
| Mother’s Drug Use Before Pregnancy (quantity & type) | X |  |  |  |  |  |  |  |
| Mother’s Reasons for Change in Drug Use During Pregnancy | X |  |  |  |  |  |  |  |
| Mother’s Drug Use During Pregnancy | X |  | X |  |  |  |  |  |
| Mother’s Change in Cigarette Use During Pregnancy | X |  | X |  |  |  |  |  |
| Mother’s Alcohol Use During Pregnancy | X |  | X |  |  |  |  |  |
| Mother’s Change in Alcohol Use During Pregnancy | X |  | X |  |  |  |  |  |

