**11. STUDY TREATMENT vigilanceSafety Reporting**

**11.1 Adverse Event (AE)**

An AE is any untoward occurrence which does not necessarily have a causal relationship with the trial treatment. An AE can therefore be any unfavourable and unintended sign, symptom, or disease temporally associated with the trial treatment, whether or not considered related to the treatment.

AEs will be collected from the time of randomisation until the final 48-month follow-up visit for each participant.

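### SAE reports depend on awareness, with no common enquiry in both arms, so any high-versus-low reading of SAEs is at risk of detection bias

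*Protocol*

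**What the plan says.** Section 11.1 sets the collection window: "AEs will be collected from the time of randomisation until the final 48-month follow-up visit for each participant". Section 11.5 gives the only stated trigger for a serious event: "SAEs will be reported via the eCRF within 24 hours of becoming aware of the event". It also refers to separate SAE reporting instructions, which are not at hand. Section 11 does not say who must become aware, or by what enquiry.

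Contact differs between the arms because contact is the treatment. Section 7.1: "The high treatment group will receive twice monthly home visits, lasting approximately one hour". Section 7.2: "The low treatment group will also have access to a support worker who can help them avail of community services if needed". Under section 10.4 all groups are interviewed at 6, 12, 18, 24, 36 and 48 months.

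Section 10.4 says that Table 1 "lists the complete set of instruments which will be collected over the 8 data assessment point". The table has no adverse-event item. The child's hospital inpatient visits are asked about at all six waves from 6 to 48 months. For the mother, the row "Health Services Use in last 12 months" is marked at baseline, 18 and 36 months only. Maternity records are collected after birth, and children's hospital records once the child is at least 4.

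On use of the data, section 17.3 has the DMEC review SAE reports, and section 12.2 describes all statistical analysis as comparing high with low treatment (and both with the external group).

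**The concern.** When a report depends on someone hearing of an event, the number and timing of reports follow the amount of contact. Here one arm is scheduled to be seen about every two weeks and the other at intervals of 6 to 12 months, apart from support given on demand. With no true difference in risk, more events could come to light in the high-treatment arm, and sooner. A DMEC reading the reports by arm could then see a harm signal that comes only from contact, or fail to see a real excess in the low-treatment arm. An analyst cannot recover events that were never elicited, so this has to be settled in data collection.

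**Working it through.** The protocol gives no SAE rate, detection rate or safety power, so there is no figure of its own to reproduce. The contact counts and waits below assume that visits are delivered as planned. They leave out visits before birth and after 48 months.

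**1. Scheduled contacts, birth to 48 months** (sections 7.1, 7.2, 10.4 and Table 1)
- High: 2 visits × 48 months = 96, plus 6 interviews = 102.
- Low: 6 interviews. Support-worker contact is on demand and has no schedule to count.
- Ratio: 102 / 6 = 17. With the 3-month column of Table 1 (maternal intelligence test): 103 / 7 = 14.7.

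**2. Mean wait from an event to the next scheduled contact.** For events spread evenly over 48 months, mean wait = Σ(gap²/2) / 48.
- High, 96 gaps of 0.5 month: 96 × 0.125 / 48 = 0.25 month.
- Low, four gaps of 6 and two of 12: (4 × 18 + 2 × 72) / 48 = 216 / 48 = 4.5 months.
- Low with the 3-month contact: (2 × 4.5 + 3 × 18 + 2 × 72) / 48 = 207 / 48 = 4.3 months.

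This is delay. It becomes loss only if an event is never asked about, is forgotten, or is recorded at interview but not passed to the SAE file.

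**3. What the interviews cover**
- *Child admissions:* asked in both arms at every wave, with a 6- or 12-month look-back, so 0-48 months is covered. Children's hospital records offer a check. No passage links either source to SAE reporting.
- *Maternal admissions, by row label:* the health-since-birth row at 6 months covers 0-6. The 12-month services row covers 6-18 (asked at 18) and 24-36 (asked at 36). Uncovered: 18-24 and 36-48, that is 6 + 12 = 18 of 48 months (37.5%).
- *How far this depends on reading the labels:* if the open row on important events since the last interview (asked at 48 but not at 24 months) is taken to elicit admissions, 6 of 48 months remain (12.5%). If general health and GP visits (both asked at 24 and 48 months) are also taken to do so, none remain. Table 1 gives labels, not question wording, so the true figure cannot be fixed.

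**4. Illustration only.** Assumptions, not document figures: equal true SAE risk in both arms; 95% detected in the high arm; 85%, 70% or 50% detected in the low arm.
- Apparent risk ratio: 0.95/0.85 = 1.12; 0.95/0.70 = 1.36; 0.95/0.50 = 1.90.
- Chance of a significant excess in the high arm, n = 100 per arm, two-sided 5%: Φ[(p₁ − p₂ − 1.96·se₀)/se₁], with se₀ pooled and se₁ unpooled. At 20% true risk and 70% detection: p₁ = 0.19, p₂ = 0.14, se₀ = 0.0525, se₁ = 0.0524, giving Φ(−1.01) = 16%. At 85% it is 6%, and at 50% it is 44%. The nominal rate in that direction is 2.5%.
- Over true risks of 10% to 30% the range is 4% to 7% (85% detected), 9% to 23% (70%) and 23% to 64% (50%).

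Modest under-detection matters little; heavy under-detection matters a good deal. The protocol does not show which applies.

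**The case against.** The other side has real force.

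- **No by-arm SAE test is specified.** Section 11 describes case-level handling, and tabulation by arm may be left to the SAP or the DMEC charter. This stands. It does not remove the issue, because sections 12.2 and 17.3 leave a by-arm reading open, and neither an SAP nor a charter can supply events that were not elicited.
- **Mentors are nowhere named as reporters.** If only blinded research staff report, from identical interviews, ascertainment is the same in both arms. This stands, and it is why the point is conditional. The protocol does not say that this is the arrangement.
- **The SAE reporting instructions may settle how events are found.** Possible. Section 11.5 cites them for rapid reporting, and they cannot be checked here.
- **Delay is not loss.** This stands for child admissions, the best-covered category.
- **The maternal gap rests on row labels.** This stands; the range from 0 to 18 months in the working reflects it.

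A reader might infer that the by-arm safety comparison is already biased, that the high arm will show more SAEs, or that low-treatment families are seen only at interviews. The documents support none of these. No comparison is laid down, the route from mentor to SAE file is not stated, and the low arm has a support worker on demand.

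**Conclusion.** The point holds as a risk. Section 11 makes SAE reports depend on awareness and sets no common enquiry, between arms whose scheduled contact differs by a factor of roughly 15 to 17. If mentors' knowledge reaches the SAE file, any high-versus-low reading of SAEs is open to detection bias, most likely against the programme. Its size cannot be derived from the protocol, and the illustrated risk ratios and false-signal rates rest wholly on assumed detection. Exposure is least for child admissions and greatest for maternal admissions at 18-24 and 36-48 months, subject to the actual question wording. This is a safety-data point that is cheap to improve.

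**What to change.** In section 11 and Table 1:

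1. State that the interview admission items (mother and child) and the hospital records already collected feed the SAE file in both arms.
2. Ask the existing maternal health-services item also at 24 months (6-month recall) and at 48 months (12-month recall).
3. Add a source-of-report field to the SAE form.
4. Limit any by-arm SAE comparison to events elicited identically in both arms. List events notified by mentors or support workers separately, and keep reporting them under the existing 24-hour rule.

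The cost is a slightly longer interview at two waves, one form field and some protocol wording. Events known only through programme staff leave the comparative table, though they are still reported. Some gaps remain: the added item would not capture maternal deaths or SAEs without admission, and the records named in section 10.4 (maternity and children's hospital) would not verify later maternal admissions.

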**11.6 Definition of a Serious Adverse Reaction (SAR)**

A SAR is defined as a SAE that is judged to be related to the trial treatment.

**11.7 Definition of Unexpected and Related Serious Adverse Events**

A Related and Unexpected Serious Adverse Eventsis an Adverse Event that is classed asserious, is suspected to be caused by the trial treatment and is unexpected i.e. not listed as an ‘expected SAE’ in this protocol.

**11.8 Reporting of Related and Unexpected Serious Adverse Events**

All Related and Unexpected Serious Adverse Events will be notified to the Research Ethics Committee (REC) and the Sponsor within 15 days of becoming aware of the event.

Follow up of participants who have experienced a Related and Unexpected Serious Adverse Event should continue until recovery is complete or the condition has stabilised.

**11.9 Annual reporting of SAEs**

Annual safety reporting will be included in the annual progress report sent to the REC, on the anniversary of Ethics approval each year.

1. **STATISTICAL ANALYSES**

**12.2 Data Analysis**

The primary analysis will be by intention to treat (ITT). All statistical analysis will involve comparing both treatment group A (high dosage) to treatment group B (low dosage), and groups (A+B) to control group C (external comparison group). A simple analysis of the randomised experiment will tell us if the PFL programme had a causal effect. Then, by modelling the possible relationships between the independent, mediating, and moderating variables and the outcome variable, we will investigate the antecedents and consequences of any mediating process measured, and test whether the independent variable directly, or indirectly through mediating variables, causes changes in school readiness (Shadish, Cook & Campbell, 2002). Hence causal modelling will allow us to identify the basis for any proportional improvements in outcomes. However, the reliability of both the RCT effect size and the causal modeling will critically depend on 1) power effects and 2) sample size (attrition).

**Estimation of treatment effects:** T-tests from OLS regressions on the continuous outcomes and chi-squared tests from logistic regressions on the binary outcomes will be estimated. Secondly, permutation-based hypothesis testing will be used as an alternative method of assessing the statistical significance of the observed treatment effects. Permutation testing is more suitable than standard bivariate tests, such as t-tests, as it does not depend on distributional assumptions and thus facilitates the estimation of treatment effects in small samples (Ludbrook and Dudley, 1998). A number of simulation studies have found that permutation testing has superior power advantages over parametric t tests, particularly if the data are skewed and the degree of skewness is correlated with the size of the treatment effect (e.g. Hayes, 1996). A permutation test relies on the assumption of exchangeability under the null hypothesis. If the null hypothesis is true, which implies that the programme has no impact, then taking random permutations of the treatment indicator does not change the distribution of outcomes for the high or low treatment group.

Permutation tests calculate the observed test statistic that is generated by comparing the mean outcomes of the high and low treatment groups. Next, the data are repeatedly shuffled so that the treatment assignment of some participants is switched between the groups. The *p*-value for the permutation test is computed by examining the proportion of permutations that have a test statistic more extreme than the observed test statistic. In this study, we will use permutation tests based on 100,000 replications, to estimate the programme’s impact. We will report *p*-values from one-sided tests. Effect sizes will be calculated using Cohen’s *d* for continuous variables and marginal effects (ME)for binary variables.

**Differential Attrition:** Due to differential attrition, the estimation samples at each data collection point may not be representative of the original randomized sample. This may bias the estimation of treatment effects if the type of participants who drop out of the study or do not complete a particular assessment differ across the groups. An inverse probability weighting (IPW) procedure will be applied to deal with this issue. This involves estimating logistic regression models predicting the probability of completing an interview at each assessment point by modelling attrition as a function of baseline characteristics. The probabilities generated from these logistic models will then applied as used as weights in the estimation of treatment effects (regression models and permutation testing) so that a larger weight is applied to participants that are underrepresented in the sample due to missing observations.

**Multiple Hypothesis Testing:** Analysing the impact of the programme on multiple outcome measures increases the likelihood of a Type-1 error and studies of RCTs have been criticized for overstating treatment effects due to this ‘multiplicity’ effect (Pocock et al., 1987). In order to assess the robustness of our results we will adjust the individual test p-values using the stepdown procedure, as described in Romano and Wolf (2005). The stepdown procedure involves calculating a t-statistic for each null hypothesis in a family of related outcomes and placing them in descending order. Using the permutation testing method, the largest absolute observed t-statistic is compared with the distribution of maximal permuted t-statistics. If the probability of observing this statistic by chance is high (p ≥ 0.1) we fail to reject the joint null hypothesis that the treatment has no impact on any outcome in the family being tested. If the probability of observing this t-statistic is low (p < 0.1) we reject the joint null hypothesis and proceed by excluding the most statistically significant individual hypothesis and test the subset of hypotheses that remain for joint significance. This process of dropping the most significant individual hypothesis continues until only one hypothesis remains. ‘Stepping down’ through the hypotheses allows us to isolate the hypotheses that lead to a rejection of the null. This method is superior to the Bonferroni adjustment method as it accounts for interdependence across outcomes.

A detailed statistical analysis plan will be prepared and signed off prior to any interim analyses.

1. **Patient and public involvement (PPI)**

The views of socio-economically disadvantaged parents have been considered during the development of this protocol. Parents will play a significant role in helping to conduct the study, monitor study progress and disseminate study findings.

Feedback from participants and service users has influenced the protocol in the following ways:

1. Planning to take a pragmatic approach to the delivery of the intervention, focusing on ensuring engagement with the primary caregiver, but also actively trying to involve both parents/carers if possible;
2. Assessment will be held in participants’ homes and will be flexibly timed, offering evening and weekend sessions where necessary;
3. The intervention format will be more flexible so that sessions can be held with an individual parent or with parents/carers together.

A Parent Advisory Group (PAG) will be set-up to oversee study progress throughout the duration of the trial. Members of the PAG will be asked to comment on participant information before the start of the study and will also be sent a draft version of the full study report, summary reports of the study findings for participants, and all other aspects of the dissemination strategy.

1. **REGULATORY, ETHICAL AND LEGAL ISSUES**

The study will be conducted in accordance with the Declaration of Helsinki, the Data Protection Act and the guidelines laid down by the International Conference on Harmonisation for Good Clinical Practice (ICH GCP E6 guidelines).

